
### Safety assessments

If any unexpected adverse events (AEs) related to interventions happened, it will be documented in details and given treatment options for rescue at once by research assistants and therapists at each CHC. If serious AEs happened, a decision on whether the participant needs to withdraw from the study will be made by the principal investigator and ethics committee. The causality between AEs and the exercises will also be analyzed.

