### Intervention group

The participants in the intervention group will accept a 12-week Tai Chi Yunshou exercises training with a frequency of 5 days per week and 60 minutes one day. The training scheme originated from the 24 forms simplified Tai Chi exercise, which is recommended as the popularity health sport by General Administration of Sport of China (Figure 2) [28,29]. Five qualified coaches who have engaged in the physical education over 5 years will teach the participants of correct Tai Chi Yunshou postures in CHCs during the whole intervention period. Each session included a 15 min warm-up time, then training 45 min continuously. The coach could adjust the length of the training time based on patients’ personal situation, and allocate properly. Individuals who have difficulty in completing the exercise continuously will be allowed to finish intermittently. But each session must last at least 15 min. All patients have 5 min to rest after training. One supervisors will be in charge of the management of training spot to guarantee the quality of Tai Chi Yunshou exercise training.

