### Follow-up

All participants will enter 12-week unsupervised follow-up period right after the end of intervention. Telephone follow-up will be performed once a week and home visits once a month. Throughout the follow-up period, patient’s current physical and mental status, rehabilitation exercises usage, the quality of life, compliance behavior and usage of drug will be recorded.

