### Statistical analysis

The data will be analyzed at the patient level by a statistician working in the Center of Evidence-based Medicine of FJTCM, who is not involved in this trial. The primary analysis will compare the proportion of patients improved of balance function at the 12-week after treatment using a mixed-effects logistic regression model in the intention-to-treat sample (including all randomized patients). Treatment condition (intervention versus control) will be treated as a fixed effect. Baseline severity of balance dysfunction will be included as a covariate and variation among patient clusters (recruited by the same CHCs) will be modeled through random effects. Potential confounding for other measured cluster-level variables such as population size will be adjusted. Continuous outcomes will be analyzed according to the same scheme, but in linear rather than logistic regression models. Item-level missing data in psychometrically sound instruments will be treated in compliance with the corresponding manuals. If no recommendations are available, the expectation-maximization (EM) algorithm will be used to impute up to 30% of missing item responses. Unit-level missing data (patients not providing data for a whole measurement point due to dropping out of the study, for example) will be imputed via the EM algorithm using existing information from the baseline assessments. Further secondary analyses will include analyses in the per-protocol (completer) sample to test the robustness of the primary findings. No interim analysis is planned. Intervention-related data are stored and analyzed separately. All analyses will be implemented using SAS software (version 8.2, SAS Institute, Cary, NC, USA).

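### After a serious adverse event the stated decision is whether the patient leaves the study, not whether the exercise stops, so some avoidable post-event outcomes may be lost

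*Protocol article*

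**What the plan says.** All references are to the protocol article.

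- **Safety assessments.** After a serious AE, "a decision on whether the participant needs to withdraw from the study will be made by the principal investigator and ethics committee". The decision is made case by case. The text does not say whether it covers all serious AEs or only those related to the exercise.
- **Intervention group.** The coach may shorten or split Tai Chi sessions, with a floor: "But each session must last at least 15 min". This is the only relaxation of training stated for that arm.
- **Statistical analysis, primary.** The comparison is of the "proportion of patients improved of balance function at the 12-week after treatment", carried out "in the intention-to-treat sample (including all randomized patients").
- **Statistical analysis, missing data.** Wholly missed visits are described as "patients not providing data for a whole measurement point due to dropping out of the study, for example". One method is given for them: such values "will be imputed via the EM algorithm using existing information from the baseline assessments".
- **Statistical analysis, robustness.** The check named is "analyses in the per-protocol (completer) sample to test the robustness of the primary findings". Completer is not defined.
- **Follow-up.** "All participants will enter 12-week unsupervised follow-up period right after the end of intervention". Whether this includes patients withdrawn after an SAE is not said. Table 3 schedules adverse event, fall and cost records through weeks 19 to 24.

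**The concern.** Stopping a treatment and leaving a trial are different decisions. A patient who has had a serious fall or a cardiac event may need to stop exercising, but can often still be assessed. An ITT analysis needs that assessment. As worded, the safety rule puts only the second decision to the principal investigator and ethics committee.

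If such a patient is withdrawn before the primary BBS, the value is filled in from information that predates the event and so ignores it. If the event set back balance, and such withdrawals are more frequent in one arm, that arm looks slightly better than it should in the ITT analysis. The completer analysis drops the same patients and errs in the same direction. Agreement between the two would therefore be no reassurance.

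These withdrawals differ from ordinary dropout because the trial itself decides them, so the missing value is partly avoidable. Withdrawal would presumably also end safety, fall and cost recording in the patients for whom it matters most, though that is inference and not stated.

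**Working it through.** **Step 1: follow one patient through the text.** The patient has an SAE in week 6, and the committee decides on withdrawal.

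1. Safety assessments: the patient leaves the study. No passage provides for stopping exercise and continuing visits, and shortened sessions are not a stop.
2. Statistical analysis: no week-12 BBS is available, so it is imputed by EM. The named source is the baseline assessments. The week-4 BBS, which Table 2 schedules, is not named as an input.
3. Robustness: on the ordinary meaning of completer, the patient is excluded.

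Neither analysis uses a post-event outcome. A patient withdrawn after the primary assessment keeps the observed primary value and is not affected on that outcome.

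**Step 2: size.** The article gives no SAE rate, arm imbalance or responder cut-off, so there is no plan figure to reproduce and the result is a range under assumptions.

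Inputs:
- Mean (SD) BBS gain 8.5 (2.8) for Tai Chi and 6.5 (3.33) for control; ICC 0.05, cluster size 25, 125 per arm, 10% dropout (Sample size).
- Assumption: improved means a gain of at least 5.8 points, with normal gains. The Primary outcome section gives 5.8 only as a detectable change, not as a responder definition.

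Reference difference:
- Tai Chi: 1 − Φ((5.8 − 8.5)/2.8) = 0.8325
- Control: 1 − Φ((5.8 − 6.5)/3.33) = 0.5832
- Difference: 0.2493, or 24.9 percentage points
- Design effect: 1 + 24 × 0.05 = 2.2
- SE = √[2.2 × (0.8325 × 0.1675 + 0.5832 × 0.4168)/125] = 0.0820, so the difference is 0.2493/0.0820 = 3.04 SE

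Let k be the net excess of such withdrawals before week 12 in one arm, t the true chance that these patients improved, q the chance that they are imputed as improved, and p the arm's true proportion.
- ITT shift = k(q − t)/125
- Completer shift = (125p − kt)/(125 − k) − p

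Planned dropouts are 0.10 × 125 = 12.5 per arm, so k = 1, 3, 5 is 8%, 24%, 40% of them. The intermediate q is the mean of the two arms, (0.8325 + 0.5832)/2 = 0.708. Shifts for an excess in the Tai Chi arm, in percentage points (SE units in brackets):

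| Case | k = 1 | k = 3 | k = 5 |
|---|---|---|---|
| ITT, upper end: q = 1, t = 0 | 0.80 (0.10) | 2.40 (0.29) | 4.00 (0.49) |
| ITT: q = 0.708, t = 0 | 0.57 | 1.70 | 2.83 |
| ITT, milder: q = 0.708, t = 0.3 | 0.33 (0.04) | 0.98 (0.12) | 1.63 (0.20) |
| Completer, t = 0 | 0.67 | 2.05 | 3.47 |
| Completer, t = 0.3 | 0.43 (0.05) | 1.31 (0.16) | 2.22 (0.27) |

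The ITT and completer shifts have the same sign, which is why the second cannot expose the first.

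For an excess in the control arm, the ITT shifts are the same size in the opposite direction. The completer shifts are then 0.47, 1.43 and 2.43 points (t = 0) or 0.23, 0.70 and 1.18 points (t = 0.3), also in the opposite direction.

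For balanced withdrawals, five per arm with the same t in both arms:
- ITT with a common imputed chance: 0
- ITT with arm-specific imputed chances: 5 × 0.2493/125 = 1.0 point
- Completer: 5 × 0.2493/120 = 1.04 points

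**The case against.** The strongest reply is that this reads a defect into the silence of a condensed article. Safety assessments is a short paragraph, and the full protocol, not shown, may separate stopping exercise from leaving the study. The text asks whether withdrawal is needed, so staying in is open. It does not say that assessments end on withdrawal, and the imputation rule is triggered by missing data, not by the committee's decision. Harm also requires several things at once: withdrawal before the primary BBS, an event that set back balance, an imbalance between arms, and a patient who could have been tested. Even then the milder ITT shift is at most 0.20 SE, and no larger at k = 3 than the 1.0 point that balanced withdrawals can give.

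Much of this stands, and it limits the finding to a minor one. The link from withdrawal to a missing BBS is a plain reading and not a stated rule, completer is undefined, and the upper end is a bound. Two things remain. First, the article does not merely omit a detail: it frames the post-SAE decision as leaving the study, and the missing-data rule then gives dropping out of the study as its example. Second, this is a rule of trial conduct. An analysis plan can improve the imputation but cannot recover assessments that were never made. If the full protocol already separates the two decisions, confirming that is enough.

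**Conclusion.** The concern holds, at low severity. On a plain reading, a patient withdrawn after an SAE and before the primary BBS contributes no post-event outcome to either the primary or the robustness analysis, although the primary analysis is described as ITT in all randomized patients.

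The effect is probably small. Under the assumed 5.8-point cut-off and normal gains, a net excess of one to five such withdrawals moves the ITT difference by 0.3 to 4.0 points (0.04 to 0.49 SE). With rare withdrawals the shift is nil or near nil, and with five in each arm it is 0 to about 1.0 point. None of these alone would overturn a 24.9-point difference. The excess and the cut-off are assumptions, since the article gives neither.

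The finding concerns only withdrawals decided by the trial after SAEs. How EM handles other dropouts is a separate matter.

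**What to change.** Reword the Safety assessments paragraph so that, after a serious AE, the principal investigator and ethics committee decide whether the patient stops the assigned exercise. Add that such patients stay in all scheduled assessments and in adverse event, fall and cost recording to week 24, unless they withdraw consent to data collection or cannot be assessed. In Statistical analysis, state that values observed after stopping exercise are used in the ITT analysis and that only visits truly missed are imputed.

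The cost is a short amendment with no new assessments. It is not quite free: three ethics committees approved the trial and recruitment has started. Staff will need some extra effort to bring patients who have stopped exercising to visits already on the schedule, and some BBS values will still be missing for patients too unwell to be tested.

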### Economic evaluation

The direct costs and indirect costs of the interventions will be investigated throughout the trial. Direct costs include the length of any hospital stay, emergency department visits, general medical treatment, visits to a specialized physician, nursing care and so on. And the number of workdays lost by participants and their families during rehabilitation will be used to assess indirect costs. All participants will be required to record their drug use, frequency of falling per week or any consumption of medical resources during the intervention period.

### Statistical analysis

The data will be analyzed at the patient level by a statistician working in the Center of Evidence-based Medicine of FJTCM, who is not involved in this trial. The primary analysis will compare the proportion of patients improved of balance function at the 12-week after treatment using a mixed-effects logistic regression model in the intention-to-treat sample (including all randomized patients). Treatment condition (intervention versus control) will be treated as a fixed effect. Baseline severity of balance dysfunction will be included as a covariate and variation among patient clusters (recruited by the same CHCs) will be modeled through random effects. Potential confounding for other measured cluster-level variables such as population size will be adjusted. Continuous outcomes will be analyzed according to the same scheme, but in linear rather than logistic regression models. Item-level missing data in psychometrically sound instruments will be treated in compliance with the corresponding manuals. If no recommendations are available, the expectation-maximization (EM) algorithm will be used to impute up to 30% of missing item responses. Unit-level missing data (patients not providing data for a whole measurement point due to dropping out of the study, for example) will be imputed via the EM algorithm using existing information from the baseline assessments. Further secondary analyses will include analyses in the per-protocol (completer) sample to test the robustness of the primary findings. No interim analysis is planned. Intervention-related data are stored and analyzed separately. All analyses will be implemented using SAS software (version 8.2, SAS Institute, Cary, NC, USA).

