### Sample size

The sample size calculation is based on a comparison between the intervention group and the control group, represented by the improvement of the Berg Balance Scale (BBS) as the main effect indicators. Our preliminary test data indicated that the means with standard deviation of the score with the intervention group was 8.5 points and 2.8 points, while 6.5 points and 3.33 points with the control group. The number of qualified participants recruited from each CHC will not be less than 25. And prior data indicate that the intra-CHC correlation coefficient is likely to be, at most, 0.05. One hundred and fourteen individuals per group are calculated according to the formula [26]:$$ n=\frac{2\left[{\left({\mu}_{\alpha }+{\mu}_{\beta}\right)}^2{\sigma}^2\right]}{\delta^2}\left[1+\left(m-1\right)\rho \right] $$with a type I error of 5% (α = 0.05) and 90% power (β = 0.10). Assuming a dropout rate of 10%, the sample size is 125 for each group and 250 in the two groups. Therefore, in order to achieve 80% power with an average cluster size of 25 patients and ICC of 0.05, 10 CHCs will be required (5 per arm).

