### Primary outcome

Balance function will be assessed with BBS, which is identified as the most commonly used assessment tool across the continuum of stroke rehabilitation [31]. The Chinese version translated by Yan Tiebin and Jin Dongmei [32] will be used. The scale measures both static and dynamic aspects of balance though l4 items. Each item is scored from 0 to 4, with a score of 0 representing an inability to complete the task and a score of 4 representing independent item completion. A global score is calculated out of 56 possible points. A difference of 5.8 points on the BBS was required to conclude with 90% certainty that patients receiving stroke rehabilitation underwent a real change in balance [33].

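### The sample size and 90% power were derived for a difference in mean BBS improvement, but the primary test is a logistic model of an undefined proportion improved

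*Protocol article*

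**What the plan says.** Three sections of the protocol article describe the primary comparison.

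- **Sample size.** The calculation compares the arms on BBS change, "represented by the improvement of the Berg Balance Scale (BBS) as the main effect indicators". The pilot figures are means with SDs: "the score with the intervention group was 8.5 points and 2.8 points", "while 6.5 points and 3.33 points with the control group". They enter a two-means formula with a design effect, "with a type I error of 5% (α = 0.05) and 90% power (β = 0.10"). The result is 114 per group, or 125 after 10% dropout, in 5 community health centres (CHCs) per arm.
- **Primary outcome.** The outcome is the BBS global score out of 56. One change figure is given: "A difference of 5.8 points on the BBS was required to conclude with 90% certainty" that a patient has really changed. The section does not call it a responder cut-off.
- **Statistical analysis.** "The primary analysis will compare the proportion of patients improved of balance function" at 12 weeks, by mixed-effects logistic regression with baseline severity as covariate and CHC as random effect. Continuous outcomes follow the same scheme in linear models.

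No section says what change counts as improved or what proportions are expected in each arm.

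**The concern.** The test labelled primary is not the test that was sized. The sample-size formula takes a mean difference and an SD, and no proportion enters it. A comparison of proportions has its own power, which depends on where the cut-off lies within the distribution of BBS change, and the article does not fix that point. Two things are at stake. The stated power cannot be read as the power of the primary analysis. And unless the cut-off is fixed in advance, it could be chosen after the data are seen, when it affects the result.

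**Working it through.** **Inputs from the Sample size section.** Means 8.5 and 6.5 (δ = 2.0); SDs 2.8 and 3.33; m = 25; ICC 0.05; α 0.05 (two-sided assumed, since sidedness is not stated); power 90%; dropout 10%.

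**1. Reproduce the plan's figure.**
- Common variance: (2.8² + 3.33²)/2 = 9.464, so SD = 3.076.
- Design effect: 1 + 24 × 0.05 = 2.2.
- Normal approximation: 2 × (1.960 + 1.282)² × 9.464 / 2² = 49.7; × 2.2 = 109.4, so 110.
- Allowing for the t distribution: 51 × 2.2 = 112.2, so 113.
- Power at 114 per group: effective n = 114/2.2 = 51.8, and two-means power is 91.1%.

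The stated 114 is thus close to a two-means result at 90% power.

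**2. Proportions implied by the same figures.** If BBS change is normal, P(gain > c) = 1 − Φ((c − mean)/SD). For c = 5.8:
- Tai Chi: 1 − Φ((5.8 − 8.5)/2.8) = 83.3%.
- Control: 1 − Φ((5.8 − 6.5)/3.33) = 58.3%.

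**3. Power of a cluster-level test.** Each trial was simulated with 5 CHCs per arm, 22 analysed per CHC (25 × 0.9 = 22.5, rounded down), ICC 0.05 on the BBS scale, and an unadjusted t-test on cluster means or proportions with 8 df. Repeat runs differ by a point or two.

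| *Improved* means a gain of | Tai Chi | Control | Power |
|---|---|---|---|
| more than 0 | 99.9% | 97.5% | about 17% |
| more than 3 | 97.5% | 85.3% | about 71% |
| more than 5.8 | 83.3% | 58.3% | about 83% |
| more than 8.5 | 50.0% | 27.4% | about 67% |
| more than 10 | 29.6% | 14.7% | about 47% |
| (difference in means) | | | 83 to 84% |

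The last row can be checked by formula. The design effect is 1 + 21 × 0.05 = 2.05 and the SE is √(2 × 9.464 × 2.05/110) = 0.594. The non-centrality is 2/0.594 = 3.37, and on 8 df power is 84%.

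**4. Second method.** This is a two-proportion normal test on n/2.2, with the ICC of 0.05 carried over to the binary outcome. For c = 5.8 at 114 per group:
- Difference 0.2493; mean proportion 0.708.
- Null term √(2 × 0.708 × 0.292) = 0.643; alternative term √(0.833 × 0.167 + 0.583 × 0.417) = 0.618.
- Power = Φ((0.2493 × √51.8 − 1.96 × 0.643)/0.618) = Φ(0.86) = 80.6%. At 125 per group it is 84.1%.

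Over the cut-offs tried, the maximum is near 6 points: 80.6% at 114 and 84.2% at 125. None reaches 90%. For 90% power the most favourable cut-off needs 150 per group (150/0.9 = 167 after dropout; 167/25 = 6.7, so 7 CHCs per arm). Counting any gain would need 1,030 per group before dropout.

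**The case against.** The strongest reply is that 5.8 points is the natural cut-off. It stands in the Primary outcome section, it describes real change, and it is the only such figure. At 5.8 the responder test loses almost nothing against the mean comparison (about 83% versus 83 to 84%). Both also exceed the 80% that the Sample size section gives in its closing sentence, after 90% earlier. A condensed article may also leave the exact cut-off to a fuller document. Most of this stands: the loss of power is material only if the cut-off lies well away from about 6. It does not remove the mismatch. The article never links 5.8 to the analysis, and supplying a cut-off later would not make the two-means calculation a calculation for proportions.

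The simulated test is also not the planned model, which is a patient-level logistic model adjusted for baseline severity. BBS change is a bounded integer rather than normal, and a t-test on cluster proportions behaves poorly when almost everyone responds. The power figures are therefore illustrative.

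Three stronger readings are tempting, but the article does not support them.
- **That there are two competing primary analyses.** Only one is labelled primary, and the sentence on continuous outcomes is not labelled secondary.
- **That the primary test has about 17% power.** That needs *improved* to mean any gain at all, which the article does not say. It is a worst case.
- **That the linear model would deliver 90%.** With 10 clusters and 8 df the mean comparison also gives only about 84%.

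**Conclusion.** The point holds as a mismatch between sizing and analysis. The 114 per group and the 90% power belong to a difference in mean BBS improvement, while the primary test compares an undefined proportion. The practical size depends on the missing definition: almost no loss at 5.8 points, moderate loss at 3 or 8.5, and severe loss at 10 points or at any gain. In the two-proportion calculation no cut-off tried reaches 90% at 114 or 125 per group. These figures rest on normal BBS change with the pilot means and SDs, an ICC of 0.05, equal cluster sizes and an unadjusted test. Baseline adjustment could shift them. The mismatch itself is read directly from the text. How much harm follows is less certain.

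**What to change.** Make the primary analysis a linear mixed model of BBS at week 12, with arm and baseline BBS as fixed effects, CHC as a random effect and a small-sample degrees-of-freedom correction for 10 clusters. This matches the quantity that was sized. Keep the logistic responder analysis as secondary, with *improved* fixed in advance, for example a gain of at least 6 points, the first whole score above 5.8.

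Keeping the responder analysis primary is also workable. The cut-off must then be fixed and the power restated for proportions: about 80 to 84% near 6 points, not 90%.

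Neither route needs new patients or measurements if the lower power is accepted. The Trial status section says recruitment has started, so the change needs a dated, documented amendment before outcome data are unblinded. The cost is that amendment and a stated power somewhat below 90%.

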## Methods/Design

### Trial design

The effect of Tai Chi Yunshou exercises for stroke patients will be assessed in a single-blind, cluster-randomized, parallel-controlled trial. Patients will be recruited from multicenter CHCs outpatient clinics. The protocol will be conducted at CHCs run by the Rehabilitation Hospital affiliated to Fujian University of Traditional Chinese Medicine (Fujian province, China), the First Affiliated Hospital of Henan University of TCM (Henan province, China) and the Second Affiliated Hospital of Shandong University of Traditional Chinese Medicine (Shandong province, China). Fujian University of Traditional Chinese Medicine (FJTCM) is responsible for training and supervising investigators in all research centers. A total of 10 community health centers (5 per arm) will be selected and randomly allocated into Tai Chi Yunshou exercise group or balance rehabilitation training group. Each community health centers will be asked to enroll 25 eligible patients into the trial. Primary and secondary outcomes will be measured at baseline and 4-weeks, 8-weeks, 12-weeks, 6-week follow-up , 12-week follow-up after randomization. A flow diagram of this trial is shown in Figure 1.

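### With 10 CHCs the treatment test has only 8 degrees of freedom, yet the CHC-level adjustment is left open-ended and nothing in the article allows for few clusters

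*Protocol article*

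**What the plan says.** The Trial design section of the protocol article fixes the number of randomised units: "A total of 10 community health centers (5 per arm) will be selected and randomly allocated". It also fixes their size: "Each community health centers will be asked to enroll 25 eligible patients into the trial".

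The Statistical analysis section makes a patient-level mixed-effects logistic regression on the proportion improved at 12 weeks the primary analysis. Treatment is a fixed effect, baseline severity is a covariate, and "variation among patient clusters (recruited by the same CHCs) will be modeled through random effects". The next sentence is "Potential confounding for other measured cluster-level variables such as population size will be adjusted". Population size is only an example. The section gives no closed list, no maximum number and no rule for choosing. Continuous outcomes follow the same scheme with linear models, so the sentence applies to them too.

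The Sample size section assumes that "prior data indicate that the intra-CHC correlation coefficient is likely to be, at most, 0.05". It works "with a type I error of 5% (α = 0.05) and 90% power (β = 0.10") from a formula with normal quantiles and a design effect.

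**The concern.** Treatment is assigned to CHCs, so its effect is judged against variation between CHCs. There are ten of these, and 250 patients do not change that. Two separate issues follow.

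- **Few clusters.** Large-sample inference in a random-intercept logistic model assumes many clusters. With five per arm the between-CHC variance is poorly estimated, and a 1.96 cut-off is too lenient.
- **Open-ended adjustment.** Each CHC-level covariate takes one of the 8 degrees of freedom. With a suitable reference distribution, covariates fixed in advance cost power and not type I error. A list left open fixes neither the cost nor the estimate.

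At stake are the true error rate of the primary test and the precision of its estimate. The sample size makes no provision for either issue.

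**Working it through.** **Inputs from the Sample size section.** BBS improvement: "the score with the intervention group was 8.5 points and 2.8 points" (mean and SD), against 6.5 and 3.33 for control. So δ = 8.5 − 6.5 = 2.0 and pooled SD = √[(2.8² + 3.33²)/2] = 3.076. Further inputs are m = 25, ICC 0.05, dropout 10% and α 0.05 (taken as two-sided, since the article does not say).

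**The plan's own figure.** Design effect = 1 + 24 × 0.05 = 2.2. The printed formula at 90% power gives 2 × (1.960 + 1.282)² × 3.076² / 2.0² = 49.72 per arm, and 49.72 × 2.2 = 109.4, so 110. Iterating with t quantiles gives 51 × 2.2 = 112.2, so 113. The stated 114 is close to this and belongs to 90% power; 80% power would need only 82 to 86. Then 114 × 1.1 = 125.4 (stated as 125), and 125/25 = 5 CHCs per arm. No step allows for 8 degrees of freedom.

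**Power on the between-CHC scale.** SE = SD × √[(2/n) × design effect].

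- All 25 per CHC (n = 125, design effect 2.2): SE = 0.577 and δ/SE = 3.465. Power is 93.4% by z and 85.7% by t on 8 df.
- 22.5 completers per CHC (n = 112.5, design effect 1 + 21.5 × 0.05 = 2.075): SE = 0.591 and δ/SE = 3.385. Power is 92.3% by z and 84.1% by t on 8 df.

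**Type I error.** The analytic value under a 1.96 cut-off is P(|t| > 1.96) on 8 − k df. The planned model was also simulated under no effect: random-intercept logistic by maximum likelihood with 15-point quadrature, one patient-level covariate, 10 × 25 patients, ICC 0.05, and k CHC-level covariates unrelated to outcome. There were 2000 runs per setting, so simulation error is about 0.5 to 0.8 points. The proportions improved (50% and 70%) and the latent-scale ICC are assumptions; the article gives no proportion.

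| k | df | critical t | z, analytic | z, simulated (50% / 70% improved) | t on 8 − k, simulated (50% / 70%) | BBS power, df loss only (22.5 / 25 per CHC) |
|---|---|---|---|---|---|---|
| 0 | 8 | 2.306 | 8.6% | 10.0% / 8.4% | 5.4% / 5.2% | 84.1% / 85.7% |
| 1 | 7 | 2.365 | 9.1% | 10.6% / 10.6% | 5.6% / 5.1% | 82.6% / 84.3% |
| 2 | 6 | 2.447 | 9.8% | 12.0% / 11.8% | 5.6% / 5.9% | 80.4% / 82.1% |
| 3 | 5 | 2.571 | 10.7% | 12.9% / 12.2% | 4.6% / 4.5% | 77.1% / 78.9% |
| 4 | 4 | 2.776 | 12.2% | 14.3% / 13.3% | 4.5% / 3.4% | 71.8% / 73.7% |

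A second simulation at ICC 0.05 agreed: about 9–10% by z with no CHC covariate, 12.6% with three, and roughly 5–6% by t on 8 − k df.

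**Chance imbalance.** The power column counts lost degrees of freedom only. If covariates that explain nothing also correlate with arm by chance, the variance grows on average by 7/(7 − k). With 25 per CHC, power is then about 79%, 69% and 56% for k = 1, 2 and 3.

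**Sensitivity to the ICC (50% improved, k = 0 to 4).**

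- ICC 0.01: z gives 6.6–7.6%; t on 8 − k gives 1.1–3.1%, which is conservative.
- ICC 0.10, above the protocol's ceiling: z gives 10.9–20.3%; t on 8 − k gives 7.0–8.1%.
- A t-test on CHC proportions stayed between 4.3% and 6.2% in every setting.

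**The case against.** The strongest reply is that the article specifies a model and not a test. It names no Wald statistic, no 1.96 cut-off and no degrees of freedom, and such detail is commonly left to a statistical analysis plan, which is not shown. The same model referred to t on 8 − k df is close to nominal at ICC 0.05. This stands. A reader might infer that the plan as written inflates type I error, but the documents support only the conditional statement.

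Three other tempting readings also go too far.

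- **That the adjustment uses up the 8 degrees of freedom.** One variable is named, which leaves 7. Baseline severity is a patient-level covariate and costs essentially none. Even four CHC-level covariates leave 4.
- **That covariates will be picked after imbalance is seen.** No such rule is stated, and the Blinding section keeps the arms coded A and B until the analysis is finished. In a worst case, taking the most favourable set from one to four candidates would raise a valid 5% CHC-level test to about 6.4%, 8.6%, 11.4% and 15.8%. That shows why a closed list is useful. It does not describe what the plan intends.
- **That the primary analysis should become a comparison of mean BBS.** Whether the endpoint should be mean BBS or proportion improved is a separate question.

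It is also fair to say that the power figures are for mean BBS improvement and not for the logistic primary analysis. The article gives no proportion from which to compute the latter.

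What survives is that the open-ended sentence is a stated commitment within the primary analysis, not an omission, and that it suits ten clusters badly. The one design calculation shown also ignores the small number of clusters.

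**Conclusion.** The point holds in conditional form. Ten CHCs give 8 between-CHC degrees of freedom, the CHC-level adjustment set is unbounded as written, and the article shows no allowance for few clusters.

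Under Wald z inference at ICC 0.05, the nominal 5% test would reject about 8–10% of the time with no CHC-level covariate and about 11–14% with one to four. With t on 8 − k df it stays near 5% (3.4–5.9%). The price is then power: on 8 df the plan's own BBS effect has about 84–86%, below the 90% used in its formula, and each CHC-level covariate lowers it further.

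These sizes assume a two-sided test, 50–70% improved, and CHC-level covariates that explain no outcome variation. A strongly prognostic covariate could repay its degree of freedom. At a much lower ICC the z-based excess shrinks.

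**What to change.** Keep the planned model and patient-level baseline severity, and change the wording in two places.

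1. **Treatment test.** State that the treatment effect is referred to t with 8 minus the number of CHC-level covariates as degrees of freedom, or is tested with a CHC-level summary or permutation test. For the linear models of continuous outcomes, state REML with Kenward-Roger or Satterthwaite degrees of freedom.
2. **CHC-level covariates.** Replace the open-ended sentence with at most one CHC-level covariate, named before unblinding (population size, for example, which leaves 7 df). Put any other CHC variables in sensitivity analyses.

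The cost is slightly wider confidence intervals, and some conservatism of the t reference if the true ICC is far below 0.05. The CHC-level test did not show that conservatism in the simulations. No change to design, recruitment or data collection is needed. The Trial status section says recruitment has begun, so the wording should be settled before the allocation codes are opened.
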